## **Title : “Community-based healthy lifestyle intervention amongst high risk individuals to prevent diabetes (Co-HELP)- a translational research.”**

---

### **ABSTRACT**

**Background:** Although recent evidence shown that lifestyle interventions are effective and can be delivered in an affordable manner in the community, more studies need to be done. This is due to the fact that more than 70% of people with diabetes live in low and middle income countries, and the largest increases in diabetes prevalence is predicted to occur in the Asian region. However, studies from developing countries are scarcely documented. Therefore, the objective of this study is to contribute to the growing body of literature on the effects of community-based lifestyle intervention among adults at high risk of type 2 diabetes.

**Methods:** This is a quasi-experimental study comparing a community-based healthy lifestyle intervention program (Co-HELP) to the usual care (UC) in high risk adults from two semi-urban communities. The population of this study is the high risk adults for type 2 Diabetes that will be recruited through the health screening in the community. The strategy of intervention is by using group-based approach, collaborative efforts with professionals in the initial stage but later on will be handled completely by community health workers and the peer educators. This is an innovative expansion of diabetes prevention program in the community setting that will determine the feasibility of Malaysia Diabetes Association as the empowered community partners.

**Outcome measures:** The primary outcome measures are change in the fasting blood glucose, 2-hour plasma glucose and HbA1C. Secondary outcome measures include weight, BMI, waist circumference, total cholesterol, triglyceride, LDL cholesterol, HDL cholesterol, systolic and

diastolic blood pressure, physical activity, diet and health-related quality of life (HRQOL). The outcomes will be analyzed at regular intervals within a period of one year.

**Conclusion:**

The finding from this study will perhaps demonstrate that a community-based lifestyle intervention administered through a local Non-Governmental Organization such as Malaysia Diabetes Association may become a promising strategy for widespread dissemination of interventions at preventing type 2 diabetes in high risk individuals.

## **1.0 BACKGROUND**

Despite significant advances in Medicine, Diabetes Mellitus remains a major global health problem[1]. The number of people worldwide with diabetes is projected to rise from 285 million in year 2010 to 439 million in 2030. Between 2010 and 2030, there will be an increase of 70% of adults with diabetes in developing countries and 20% increase in developed countries[2]. The increasing prevalence of type 2 diabetes worldwide is due to combination of factors such as population growth, increasing life span, urbanization, increasing prevalence of obesity and physical inactivity. Malaysia is similarly affected due to a major shift in the lifestyles and longevity of the population[3]. This rising trend is mirrored in Malaysia where the prevalence of diabetes amongst adults became almost doubled between 1986 and 2006. Globally, this places Malaysia at number ten amongst countries with high diabetes prevalence [2]. The diabetes prevalence rate has risen much faster than expected as shown by National Health and Morbidity Survey (NHMS); 6.3% (NHMS I-1986), 8.3% (NHMS II-1996) and later was found to be 14.9% (NHMS III-2006). Based on this prevalence, the projected number of people age 18 years old and above affected by diabetes in Malaysia is estimated at 1.49 million. One in seven adults in Malaysia is a diabetic. What is even more worrying is the fact that almost half of our population with diabetes is unaware that they have the disease[4]. Evidence also suggests that diabetes mortality and diabetes-related complications continue to increase resulting in rising disease burden in the country [5]. These realities exist despite the success of large scale health campaign to enhance diabetes awareness in the community. Mere public forums and mass-media advertisements of healthy lifestyle have not been able to stem the rising tide of diabetes as shown in the past two decades[3].

Evidence from large scale clinical trials such as the United States Diabetes Prevention Program (DPP)[6] and the Finnish Diabetes Prevention Study (DPS) [7] studies have demonstrated

that lifestyle modification intervention is effective in reducing or delaying the onset of type 2 diabetes in high risk individuals by 40% to 58%. Although compelling evidence exists, it has yet to be widely adopted at the community level. Therefore, the current challenge is for us to translate these evidences that suit our local context and able to disseminate in long term. Collaborative efforts with the existing Governmental Organizations and Non-governmental organizations (NGOs) locally may help to fill the gaps and support the sustainability of the diabetes prevention program in the country. Due to our limited resources, emphasis is given on prevention of diabetes amongst first degree relatives of diabetic patients whom are pre-diabetes. The first degree relatives become an important target group because they can influence the lifestyle of other family members. Furthermore, the community needs to act more aggressively to reduce the modifiable risk factors of diabetes by healthy lifestyle intervention.

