**Table 3: Other high risk factors for type 2 diabetes**

|                                      |                                                                                                       |
|--------------------------------------|-------------------------------------------------------------------------------------------------------|
| Family history of diabetes           | First degree relative with diabetes                                                                   |
| Waist circumference                  | $\geq 90$ cm for men and $\geq 80$ cm for women                                                       |
| Overweight                           | BMI $> 23$ kg/m                                                                           |
| Dyslipidemia                         | Either High Density Lipoprotein (HDL) cholesterol $< 0.9$ mmol/L or Triglycerides (TG) $> 1.7$ mmol/L |
| Hypertension                         | Blood pressure $> 140/90$ mm/Hg or on medication                                                      |
| Pre-existing cardiovascular diseases | Ischemic heart disease, cerebrovascular disease, peripheral arterial disease                          |
| Physically inactive                  | Sedentary work                                                                                        |
| High risk women                      | Women with history of polycystic ovarian syndrome (PCOS)                                              |

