**5.5 Recruitment of high risk adults**

Adults with high risk of developing type 2 diabetes will be invited to attend community-based screening and education program. The participants were recruited from general population through presentations at community-halls, mosques, as well as through media exposure like radio and Malaysian Diabetes Association website, brochures, banners, posters and healthcare providers. Screening of the high risk adults will be done in cooperation with Malaysian Diabetes Association staffs. All people attending the screening program will receive pamphlets regarding diabetes, risk factors, healthy food choice, exercise and etc. The screening tools that will be used are among the easy to perform, inexpensive, non invasive and able to sustain in the community (i.e.; Diabetes risk score questionnaire, capillary plasma glucose, weight and height for Body Mass Index (BMI), waist circumference and blood pressure). First they will have to complete the screening questionnaire. A drop of whole blood by finger prick will be done to assess Random Blood Glucose for people with  $\text{BMI} \geq 23 \text{ kg/m}^2$ . Asymptomatic individuals with Random Blood Glucose  $\geq 6.0 \text{ mmol/L}$  will be inform that they are at risk of developing diabetes and are potentially eligible for the study. Participants will be given an appointment date for baseline investigation at different dates to avoid contamination.

During baseline investigation, the participants will be assessed for Fasting Venous Plasma Glucose (FPG) and or Oral Glucose Tolerance test (OGTT). The algorithm of the screening process and diagnostic values will be based on Clinical Practice Guidelines by Ministry of Health Malaysia on Management of Type 2 Diabetes Mellitus, 4th edition 2009[40]. People with fasting plasma

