## **5.6 Allocation of participants**

The study participants will be allocated to the intervention or control group depending on which community they were enrolled at the time of the baseline screening.

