## **5.10 Case definition**

### **i) Inclusion criteria**

Participants are eligible if they live or work within the community area, age between 18- 65 years old, able to read and understand Bahasa Malaysia or English language, are at risk of type 2 diabetes with fasting blood glucose concentration of between 5.6 to 6.9 mmol/L, and/ or 2-hour 75 g oral glucose tolerance test concentration of between 7.8 mmol/L and 11.0 mmol/L [19], Body mass index (BMI) of between 23-39 kg/m^2 and had no contraindications to participate in weight management program or physical activity.

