## 12.0 DATA ANALYSIS

Patient demographic, clinical variables and baseline value will be compare between groups by the use of independent t-test for normally distributed variables and Mann Whitney test for non-normally distributed variables. Chi-square test will be use for discrete variables. The analysis will be done according to the intention-to-treat (ITT) principle. The missing values will be replaced by

the last readings carried forward. General Linear Model repeated measures ANOVA will be conducted to examine the changes overtime within-groups and between-groups. In the repeated measures model, the baseline value of co-morbidities, medication used, smoking and alcohol consumption were used as covariates in analysis for lipid profiles and blood pressure measurements. The outcome results from baseline to follow up at 6 months and 12 months will be presented as mean group differences, 95% confidence interval, p value and partial eta squared. A p-value of  $<0.05$  was considered statistical significant and effect size as proposed by Cohen (1998) were (0.01= small effect, 0.06= moderate effect and 0.14= large effect [65]. All statistical analysis will be performed using the SPSS software version 19.0 (SPSS Inc, 2009, Chicago, Illinois)

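### Several members of one household may enrol without being identified, while the sample size and the planned analysis treat all participants as independent, so standard errors may be somewhat too small

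*Protocol*

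**What the plan says.** - **Families.** Section 1.0 gives a reason for interest in relatives: "The first degree relatives become an important target group because they can influence the lifestyle of other family members".
- **Recruitment.** Section 5.5 describes an open approach through shared local venues and media: "The participants were recruited from general population through presentations at community-halls, mosques".
- **Eligibility.** Section 5.10 begins "Participants are eligible if they live or work within the community area" and then sets individual criteria on age, language, glucose, BMI and fitness to take part. Neither the inclusion nor the exclusion list restricts enrolment to one person per household.
- **Allocation.** Section 5.6 assigns the arm "depending on which community they were enrolled at the time of the baseline screening".
- **Data recorded.** The variables in section 8.0 include family history of diabetes, which describes a person but does not link participants to each other. The collection schedule in Table 8 has a socio-demography questionnaire at screening and names no household field.
- **Sample size.** Section 5.8 compares two means for each of three indicators and takes the largest result, 122 per group (244 in total), from physical activity.
- **Analysis.** Section 12.0 states: "General Linear Model repeated measures ANOVA will be conducted to examine the changes overtime within-groups and between-groups". No household or family term is named.

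**The concern.** Spouses, siblings, or parents and adult children who join together may change together. The protocol itself says that family members influence each other's lifestyle, and section 2.1 describes a strong genetic component to diabetes. In the intervention arm, Table 5 includes sessions on grocery shopping, cooking methods and recipes, which act on meals that people living together may share.

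A repeated-measures ANOVA allows for correlation between visits of one person, but not between two people in one household. If co-enrolled members are in the same arm and their changes are positively correlated, the between-arm standard error is understated. The stated 5% error would be exceeded, and the sample size would deliver less power than calculated. Because no identifier is listed, nobody could later adjust for this or even count the affected pairs.

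**Working it through.** **1. Does the plan's sample size assume independence?**

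Inputs are from the table in section 5.8, with 80% power and alpha 0.05 (sidedness not stated; two-sided assumed). The formula is n per group = 2(1.960 + 0.842)² s² / d², with s² = (SD1² + SD2²)/2.

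- Fasting glucose: d = 1.8 − (−4.3) = 6.1; s² = (13.1² + 11.3²)/2 = 149.65, s = 12.23; n = 63.1, so 64 (stated 64).
- Weight: d = 3.8 − 1.4 = 2.4; s² = (5.2² + 4.1²)/2 = 21.93, s = 4.68; n = 59.8, so 60 (stated 60).
- Physical activity: d = 46.6 − 17.9 = 28.7; s² = (63.8² + 95.5²)/2 = 6595.3, s = 81.21; n = 125.7, so 126 (stated 122). Taking the simple mean of the two SDs, 79.65, a t-test with 122 per group has 80.0% power, close to the stated basis.

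Two of the three figures are reproduced with no design effect, and the third is near. The plan does assume independence.

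**2. Effect of co-enrolled pairs**

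Let a share f of an arm's n participants be enrolled as household pairs in that arm, with correlation r in change. There are nf/2 pairs, so the variance of the arm total is nσ² + 2(nf/2)rσ² = nσ²(1 + fr). The design effect is therefore DE = 1 + fr, the same in both arms if f and r are the same.

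- Correct interval width relative to planned: √DE
- Actual two-sided error: 2[1 − Φ(1.96/√DE)]
- Power: Φ[d / (s√(2·DE/n)) − 1.96]

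The protocol gives neither f nor r. The values below are assumptions. Fasting glucose is shown at 122 per arm and after 30% loss (122 × 0.7 = 85.4 per arm).

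| f | r | DE | Width factor | Actual error | Glucose power, 122 | Glucose power, 85.4 | Activity power, 122 |
|---|---|---|---|---|---|---|---|
| 0 | any | 1.00 | 1.000 | 5.0% | 97.3% | 90.3% | 78.8% |
| 0.1 | 0.1 | 1.01 | 1.005 | 5.1% | 97.2% | 90.0% | 78.4% |
| 0.2 | 0.3 | 1.06 | 1.030 | 5.7% | 96.6% | 88.6% | 76.5% |
| 0.4 | 0.3 | 1.12 | 1.058 | 6.4% | 95.7% | 86.8% | 74.2% |
| 0.4 | 0.5 | 1.20 | 1.095 | 7.4% | 94.5% | 84.5% | 71.2% |

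**3. Outside that range**

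With 60% of participants in pairs and r = 0.5, DE = 1.30 and the error is 8.6%; glucose power is 92.7% at 122 per arm and 81.5% after loss. For triples, DE = 1 + 2fr; at f = 0.4 and r = 0.5 this is 1.40, with error 9.8%. Nothing in the protocol suggests that such values are likely.

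**The case against.** **The protocol does not recruit families.** A reader might infer from section 1.0 that relatives are the enrolled population and that joint enrolment is therefore expected. The documents do not support this. The emphasis there is on relatives of people with diabetes, and people with diabetes are excluded by section 5.10, so that particular pair cannot both enrol. No diabetic relative is required for eligibility, and family history is only one of several risk factors in Table 3. The sentence makes correlation within families plausible; it gives no co-enrolment rate. This objection stands.

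**Joint eligibility may be uncommon.** Section 2.3 and Table 2 put pre-diabetes at about 4-5% on a single criterion. Suppose, as an illustration, three other adults per household, all screened, each with a 5-10% chance of eligibility. Then f = 1 − 0.95³ = 0.14 to 1 − 0.90³ = 0.27, and with r = 0.3 the error is 5.5-5.9%. Familial aggregation would raise f; incomplete attendance and the other entry criteria would lower it. The objection limits the size but does not remove the point.

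**The mechanism is uneven.** Shopping and cooking feature in the titles of only three of twelve sessions (4, 5 and 9), and only the intervention arm receives them. Equal correlation in both arms is an assumption. Also, people may enrol where they work, so some households could straddle the two arms; correlation across arms would act in the opposite direction.

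**The analysis plan may deal with it.** The choice of standard error is often left to a statistical analysis plan, and the flow chart in section 5.9 is not shown. However, no later plan can adjust for household unless membership has been recorded.

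**Conclusion.** The point holds as a conditional one. The visible text neither limits nor records household co-enrolment, and both the sample size and the named analysis assume independence. Household members enrolled in the same community fall in the same arm, so positive correlation would understate the between-arm standard error. Over the assumed range (10-40% in pairs, correlation 0.1-0.5) the effect is small to modest.

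Two stronger readings are not supported. First, one cannot say that the intervals and p-values **are** too favourable; that depends on two quantities the protocol does not give. Second, one cannot say that the primary outcomes lose their power. Fasting glucose, the only primary outcome with sizing inputs, stays at 84.5% or more over the range even after 30% loss. The power shortfall concerns physical activity, a secondary outcome, which starts at 78.8% before any clustering.

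Nor would a household term restore a true 5% error rate. With one community per arm, community and treatment are fully confounded. Delivery in groups of up to 20 adds clustering in the intervention arm alone: 1 + 19 × ICC, which is 1.19 at an assumed ICC of 0.01 and 1.95 at 0.05. These are separate and larger issues.

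**What to change.** 1. Add a household identifier to the socio-demography questionnaire already taken at screening (Table 8), and list it in section 8.0. It must be collected prospectively.
2. In section 12.0, state that between-arm comparisons will use household-cluster-robust standard errors, or a mixed model with a household random effect in addition to the participant effect.
3. Report by arm how many households contributed more than one participant, so that readers can judge whether the adjustment mattered.

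The cost is one form field, a sentence in section 12.0, and intervals about 0.5-9.5% wider over the range shown. If co-enrolment proves rare, the results will hardly change.

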## 2.0 LITERATURE REVIEW

### 2.1 Epidemiology of Type 2 Diabetes Mellitus globally and different regions

Diabetes and associated complications pose a major health-care burden worldwide. It also presents the major challenges to public health and national economies[8]. The number of people developing Type 2 diabetes is rising dramatically worldwide. This is evident from findings of a series of global estimates of current and predicted future prevalence of diabetes [9-12] as shown in table 1.

**Table 1: Estimates of current and projected global prevalence of diabetes in adults**

|                   | King et al.
(1998) |                     | Int. Diabetes
Fed.(IDF) (2003) |                     | Wild et al.
(2004) |                     | Shaw et al.
(2009) |                     |
|-------------------|-------------------------------|---------------------|-------------------------------------------|---------------------|-------------------------------|---------------------|-------------------------------|---------------------|
| Adults     | Current
(1995)             | Projected
(2025) | Current
(2003)                         | Projected
(2025) | Current
(2000)             | Projected
(2030) | Current
(2010)             | Projected
(2030) |
| Prevalence | 4%                            | 5.4%                | 5.1%                                      | 6.3%                | 2.8%                          | 4.4%                | 6.4%                          | 7.7%                |

|                |                |                |                |                |                |                |                |                |
|----------------|----------------|----------------|----------------|----------------|----------------|----------------|----------------|----------------|
| Numbers | 135
million | 300
Million | 194
million | 334
million | 171
million | 366
million | 285
million | 439
Million |
|----------------|----------------|----------------|----------------|----------------|----------------|----------------|----------------|----------------|

---

Based on current trends, it was predicted that the population of diabetes will swell up to a staggering 439 million by the year 2030, of which almost half of that will be from the South Asia and Western Pacific Region. Every region will have an increase in numbers as well as excess of adult population growth, thus total number of diabetes are likely to increase by 50% over the 20 years [12]. The varying prevalence rates for Type 2 DM were observed in different parts of the world which reflects the underlying differences in ethnicity, demography and social risk factors such as lifestyle, diet, obesity prevalence and physical inactivity [13].

About 80% of people with diabetes are in developing countries, with Asia being the major site of rapidly emerging diabetic epidemic[11]. One of the hallmarks of diabetes in Asian countries is the rapidly increasing prevalence of young-onset diabetes (people younger than 44 years old)[8]. Factors that have contributed to the epidemic of obesity and young-onset diabetes are the rapid transition in dietary habits, reduced physical activity, changing pattern in leisure activities, longer working hours and decreasing sleep hours[14]. Type 2 diabetes has a strong genetic component and most Asian patients have first-degree relative with diabetes[15]. Prevalence estimates (standardized to world age) of diabetes and impaired glucose tolerance in all Asian countries are high and are expected to increase further during the next two decades[8].

## **2.2 Epidemiology of Type 2 Diabetes Mellitus in Malaysia**

Malaysia is similarly affected due to a major shift in the lifestyles and longevity of the population[3]. This rising trend is mirrored in Malaysia where the prevalence of diabetes amongst adults became almost doubled between 1986 and 2006. The diabetes prevalence rate has risen much faster than expected as shown by National Health and Morbidity Survey (NHMS); 6.3% (NHMS I-

1986), 8.3% (NHMS II-1996) and later was found to be 14.9% (NHMS III-2006). Based on this prevalence, the projected number of people age 18 years old and above affected by diabetes in Malaysia is estimated at 1.49 million. One in seven adults in Malaysia was a diabetic. What is even more worrying is the fact that almost half of our population with diabetes is unaware that they have the disease[4]. The status of Diabetes Mellitus in Malaysia for the past two decades is shown in Table 2.

